### Informed consent and patient confidentiality

All participants will be given detailed oral and written information about the trial. Consent forms describing in detail the study medication/intervention(s), study procedures and risks will be given to each participant and written documentation of informed consent is required prior to starting study medication/intervention. Participants may withdraw consent at any time during the course of the trial.

All participant-related information including clinical records, laboratory specimens, evaluation forms, reports, will be kept strictly confidential. All records will be kept in a secure, locked location and only research staff will have access to the records. Participants will be identified only by means of a coded number specific to each participant and the site’s alphabetic letter code. All computerized databases will identify participants by numeric and alphabetic codes only, and will be password protected.

### Metformin dosing

Arm 1 participants will be provided with the following recommended dose adjustments and advised to increase the dose accordingly: week 1: 500 mg once daily (QD); week 2: 500 mg BID; week 3: 500 mg three times daily (TID); week 4: 1 g BID or 500 mg QD. Participants will also be encouraged to administer their study treatment with food whenever possible to minimize the gastric intolerances. If participants are unable to tolerate an increase in dose, they will continue on the last dose tolerated.

Metformin dosing will additionally be based on renal function and dosed as follows:if creatinine clearance (CrCl) 30–60 mL/min, metformin will be reduced to 50 % of the dose or 500 mg BIDif CrCl < 30 mL/min, metformin will be stopped.

The potential side effects associated with metformin will be reviewed with each participant.

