**Methods:**

This study is a prospective 48-week single-centre, randomized, open-label, controlled trial of HIV-HCV co-infected and HCV mono-infected patients with IR (HOMA-IR ≥ 2.0) who are planning to initiate HCV antiviral therapy. Sixty participants will be recruited from The Ottawa Hospital Viral Hepatitis Clinic. Participants will be randomized in a 1:1 ratio to either arm 1, metformin 2 g (1 g twice daily) plus lifestyle, or to arm 2, lifestyle alone. The primary outcome will be the change in FibroScan® score (kPa) from baseline to week 12 (start of HCV treatment), the end of HCV treatment (week 24) and 24 weeks post HCV treatment (week 48). Secondary outcomes include changes in liver fibrosis using AST to platelet ratio index, changes in glucose and lipid levels, anthropometric measures, changes in alpha-fetoprotein levels, patient acceptability, and changes in dietary and physical activity parameters.

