### Study design and setting

This study is a prospective 48-week single-centre, randomized, open-label, controlled trial of HIV-HCV co-infected and HCV mono-infected patients with IR (HOMA-IR ≥ 2.0) who are planning to initiate HCV antiviral therapy.

Sixty (60) participants meeting eligibility criteria will be randomized in a 1:1 ratio using variable block sizes to either arm 1, metformin 2 g [1 g twice a day (BID)] plus lifestyle, or to arm 2, lifestyle alone (the control arm). Randomization will be stratified according to HIV status and according to stage of liver fibrosis (F0–2 vs. F3–4) and will be conducted utilizing a web-based randomization system. The allocations will be generated by a statistician unassociated with the study using the SAS statistical program (SAS Institute, Inc., Cary, NC, USA) and uploaded into the randomization system. A log of all transactions including date and time of randomization, stratum and treatment allocation will be recorded. The randomization system will be accessed by the study coordinator at the study site when they have identified consenting eligible participants ready to be randomized.

Arm 1 (Metformin group) will receive metformin and lifestyle treatment during a 12-week period prior to starting HCV therapy (week 0–12), during the 12-week treatment phase (week 12–24) and 24 weeks post HCV treatment (week 24–48). Participants who require > 12 weeks of HCV treatment will be excluded. If initiation of HCV treatment is delayed beyond 12 weeks, participants will continue on metformin during this time period and will receive less metformin post HCV treatment. Arm 2 (Control group) will receive lifestyle treatment alone during a 12-week period prior to starting HCV therapy (week 0–12), during the 12-week treatment phase (week 12–24) and 24 weeks post HCV treatment (week 24–48). A detailed study flow chart is depicted in Fig. 1.

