**Fig. 1 Fig1:**
[figure not shown]
Flow diagram of study processes. Sixty participants meeting eligibility criteria will be randomized in a 1:1 ratio using variable block sizes to either arm 1, metformin 2 g (1 g BID) plus lifestyle (Metformin group), or to arm 2, lifestyle alone (Control group). *Abbreviations: HCV* hepatitis, *HIV* human immunodeficiency virus, *IR* insulin resistance*, BID* twice daily, *DAA* direct-acting antiviral therapy*, kPa* kilopascals

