### Study treatment adherence

The following criteria will be used to define compliance during this study:Adherence with study treatment will be assessed based on participant-provided information and tablet count, i.e., drug accountability, during follow-up visits. Non-adherence will be considered for participants who have an average daily intake of less than 80 % of their maximum tolerated dose.Attend baseline visit and all follow-up visits.Adherence with HIV antiretroviral therapy (ART) (if applicable) and HCV antiviral therapy will be documented as standard of care.

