Baseline characteristics will be expressed as mean and standard deviation (SD) for continuous variables and percentages for categorical variables. Baseline variables to be considered include: age, gender, ethnicity, HCV genotype and viral load, HIV viral load and CD4 count (as per SOC), HbA1c, HOMA-IR, FibroScan® scores, smoking history, alcohol consumption, and illicit drug use.

Lifestyle modification will be evaluated through changes in physical activity (changes in median MET/week, percentage change in participants classified as low, medium and high level of activity) and dietary changes (change in median daily caloric intake, daily consumption of fat, protein, carbohydrates and micro/macro nutrients). Linear regression adjusted for baseline score will be used to compare the outcome at week 48 between groups. Mixed-effects regression analysis will also be used to compare the trend over time between groups.

Data will be collected on liver-related complications (progression of liver fibrosis stage, HCC, transplantation) and mortality. We anticipate that the event rate will be low given the small sample size and short duration of follow-up.

Subgroup analyses will be conducted based on SVR to compare the effect virological response influences liver fibrosis and the benefit of metformin in reducing progression of fibrosis. Subgroup analyses will also be conducted based on HIV status to compare the influence of HIV infection on progression of liver fibrosis and benefit of metformin in reducing the progression of fibrosis.

Subgroup analyses based on metformin doses (full dose versus not) in the metformin group and weight loss in patients in both treatment arms will also be conducted. These additional analyses will be useful in determining if lower doses can achieve the same benefit and the impact that potential weight loss associated with this medication may have on steatosis and improving liver outcomes respectively.

Subgroup analyses will also be conducted based on end of study HOMA-IR score (<2 vs. > 2) to evaluate if the benefits of metformin are dependent or independent of the insulin-sensitizing effects of this treatment.

As a sensitivity analysis, we will also consider using multiple imputation techniques to impute missing data for the primary outcome at 48 weeks. Linear regression adjusted for baseline score will then be used to compare the groups.

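### Metformin titration: the second week-4 option, 500 mg once daily, is a quarter of the 2 g/day arm 1 dose and reverses the titration

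*Protocol article*

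**What the plan says.** The article gives the arm 1 dose consistently in three places. The Abstract (Methods) has "metformin 2 g (1 g twice daily) plus lifestyle", Study design and setting has "metformin 2 g [1 g twice a day (BID)] plus lifestyle", and the Fig. 1 legend repeats it.

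Metformin dosing sets out the route to that dose. Participants receive a schedule and are "advised to increase the dose accordingly": 500 mg once daily in week 1, twice daily in week 2, three times daily in week 3, and then "week 4: 1 g BID or 500 mg QD". QD is spelled out as once daily at the week-1 step and again under Abbreviations.

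The same section has two rules for a lower dose. For participants who cannot tolerate an increase, "they will continue on the last dose tolerated". For creatinine clearance of 30–60 mL/min, the dose is halved or set to 500 mg twice daily; below 30 mL/min metformin stops.

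Two later provisions depend on the dose taken. Under Study treatment adherence, "Non-adherence will be considered for participants who have an average daily intake of less than 80" % of the maximum tolerated dose. Statistical analysis plans "Subgroup analyses based on metformin doses (full dose versus not) in the metformin group".

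**The concern.** The two week-4 options are joined as equal alternatives but differ fourfold. The first completes the titration at the arm 1 dose. The second, read as the article defines it, sends the participant back to the week-1 starting dose in a schedule meant to rise.

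This is part of the experimental-arm regimen, not background text. Anyone who follows the second option as written is under-dosed. If that continued, the participant could meet the non-adherence definition while doing what the schedule says. The same participant could also be counted as not on full dose because of wording rather than tolerance. The dose subgroup is meant to show whether lower doses achieve the same benefit, so low doses that arise from wording would blur it.

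**Working it through.** **Daily doses.** Daily dose = unit dose × administrations per day, with once daily = 1, BID = 2 and TID = 3. All inputs come from Metformin dosing; the 2000 mg/day target comes from Study design and setting.

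| Step | Calculation | mg/day | Share of 2000 |
|---|---|---|---|
| Week 1 | 500 × 1 | 500 | 25 % |
| Week 2 | 500 × 2 | 1000 | 50 % |
| Week 3 | 500 × 3 | 1500 | 75 % |
| Week 4, first option | 1000 × 2 | 2000 | 100 % |
| Week 4, second option | 500 × 1 | 500 | 25 % |

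The first option reproduces the stated arm 1 dose. The second does not. It lies 1 − 500/1500 = 67 % below week 3.

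**Could another rule explain 500 mg once daily?**
- Intolerance: a participant who fails the week-4 step stays on 500 mg three times daily, or 1500 mg/day. The rule gives 500 mg/day only to someone who never got past week 1.
- Renal function: half of 2000 mg, or 500 mg twice daily, is 1000 mg/day. Neither is 500 mg once daily.

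**Exposure over 48 weeks.** Assumptions: full tolerance, titration week n is the nth treatment week, and visits fall at the end of the named week. Weeks 1–3 contribute 500 + 1000 + 1500 = 3000 in every case.

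| Scenario | Mean mg/day | Share of plan |
|---|---|---|
| As planned | (3000 + 45 × 2000)/48 = 1937.5 | 100 % |
| Second option, corrected at week 4 | (3000 + 1 × 500 + 44 × 2000)/48 = 1906.25 | 98 % |
| Second option, corrected at week 8 | (3000 + 5 × 500 + 40 × 2000)/48 = 1781.25 | 92 % |
| Second option, never corrected | (3000 + 45 × 500)/48 = 531.25 | 27 % |

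**Adherence threshold.** A participant who is never corrected has a maximum tolerated dose of 1500 mg/day, reached in week 3. Intake is 500/1500 = 33 % from week 4 on, or 531.25/1500 = 35 % over the whole study. Both are far below 80 %. A corrected participant who then tolerates 2000 mg/day averages 1906.25/2000 = 95 % (week-4 correction) or 1781.25/2000 = 89 % (week-8 correction). Both are above 80 %.

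**The case against.** The best reply is that this is a slip in a frequency abbreviation. The 500 mg steps run once, twice and three times daily, and a fourth administration gives 500 × 4 = 2000 mg/day, exactly the dose it is paired with. The correct option comes first in the same phrase, and the target is unambiguous elsewhere. The slip is plausible, but the article never says four times daily was intended, and its list of abbreviations has none for that frequency. A reader who uses the article's own definition gets 500 mg/day.

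Three further points limit the weight of the finding, and they stand:
- The clash with the adherence rule is conditional. If intake is averaged over the whole study, correction at week 4 or 8 leaves the participant above 80 %.
- The case of no correction is a bound and not a forecast. Table 1 schedules medication review and drug accountability at weeks 4 and 8 and repeatedly afterwards, and tablet counts would show the surplus.
- The article does not say whether the dose subgroup uses the dose reached, the final dose or the average dose. A participant corrected early might still be classed as full dose.

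It is also true that the full protocol, titration sheet and dispensing instructions are not shown, so whether any participant would be given this option is unknown. None of this makes the published figure right.

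**Conclusion.** The point holds and is minor. One of the two week-4 options is a wrong dose as written: 500 mg/day, a quarter of the arm 1 target, against the direction of the titration and not explained by any other rule in the article. With correction at the week-4 or week-8 visit, 48-week exposure is 98 % or 92 % of plan; the 27 % figure applies only if the error is never noticed. These figures rest on full tolerance and the visit timing assumed above. The consequences for adherence classification and the dose subgroup arise only if the low dose persists. The sample size, alpha and primary analysis are unaffected.

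**What to change.** Ask the sponsor what frequency was intended. Unless four times daily is confirmed, delete the second option so that 1 g twice daily is the only week-4 target. If it is confirmed, keep the alternative and write the frequency in words: 500 mg four times daily.

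Check that the participant titration sheet and the dispensing instructions agree, before recruitment starts. The cost is one phrase and a check of those materials.

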### Lifestyle modification intervention

Participants in both treatment arms will be given counselling on lifestyle and dietary modifications that may help to prevent progression of liver fibrosis. Participants will be given instructions on recommended types and duration of physical activity as per Canadian Diabetes Association practice guidelines. They will be encouraged to aim for 150 minutes of moderate to vigorous aerobic exercise and two to three sessions of resistance training each week. They will additionally be provided with tips on how to become more active.

Participants will further be provided with recommendations for dietary modifications and tips for healthy eating as provided by the Canadian Diabetes Association practice guidelines. Recommended limits for alcohol consumption will be reviewed. The educational sessions will be repeated during 6-month follow-up visits.

### Primary outcome

As the primary outcome we will evaluate the change in FibroScan® score (kPa) from baseline to week 12 (start of HCV treatment), the end of HCV treatment (week 24) and 24 weeks post HCV treatment (week 48) (Table 1).

**Table 1 Tab1:** Schedule of events and data collection

Visit window			+/- 2 days						
Weeks	-4 (Screen)	0 (Baseline)	4	8	12	16	24	36	48
Informed consent	X								
Medical history	X								
Inclusion/exclusion criteria	X	X							
Drug, alcohol and smoking history	X								
Pregnancy test^a^	X	X^a^							
Medication review	X	X	X	X	X	X	X	X	X
FibroScan®^b^	X	X			X		X	X	X
Physical examination^c^ and vital signs	X	X^c^	X^c^	X^c^	X^c^	X^c^	X^c^	X^c^	X^c^
Hepatitis B serology^d^	X								
HCV RNA viral load^e^	X^e^	X	X	X	X	X	X	X	X
HCV genotype^d^		X							
HIV viral load^d,e^ (as per SOC)	X^e^	X			X		X	X	X
CD4 count^e^ (as per SOC)	X^5^	X			X		X	X	X
Hematology^f^ and chemistry^g^	X	X	X	X	X	X	X	X	X
HbA1c	X	X			X		X	X	X
Fasting insulin and glucose	X	X	X	X	X	X	X	X	X
Fasting lipids^h^		X			X		X	X	X
Inflammatory markers/research blood		X	X	X	X	X	X	X	X
TSH		X				X	X		X
AFP levels		X			X		X	X	X
2-hr OGTT		X							X
Adverse events			X	X	X	X	X	X	X
Anthropometric measures^i^	X^i^	X			X		X	X	X
Counselling on lifestyle modification		X					X		X
Block food frequency questionnaire		X					X		X
International physical activity questionnaire		X					X		X
Audit-C and illicit drug use questionnaires		X			X		X	X	X
TSQM for patient acceptability (arm 1)				X			X		X
Study drug accountability/dispensation (arm 1)		X	X	X	X		X	X	X
Birth control review	X	X	X	X	X		X	X	X

*HCV* hepatitis C, *HIV* human immunodeficiency virus, *HbA1c* glycated hemoglobin, *TSH* thyroid-stimulating hormone, *AFP* alpha-fetoprotein, *OGTT* oral glucose tolerance test, *TSQM* Treatment Satisfaction Questionnaire for Medication

^a^If randomization occurs > = 4 weeks from last pregnancy test, perform pregnancy test at baseline

^b^FibroScan® can be done at screening if necessary for inclusion; baseline test can be done on different day than rest of visit if necessary (within 4 weeks of baseline). FibroScan® window can be +/− 7 days of the week 12 visit, +/− 21 days of week 24 and 36 visits, and up to 21 days before the week 48 visit

^c^Targeted physical exam: vitals, cardiac, respiratory and abdominal exams; exam as pertinent to patient complaints

^d^Tests to be done if not already in participant medical records [hepatitis B (HBV) needs to be within 6 months of screening visit; HIV needs to be within 1 month of screening]

^e^If results available within 1 month of screening visit, no need to retest

^f^Hematology: complete blood count (CBC) with differential, platelets, international normalized ratio (INR)

^g^Chemistry: electrolytes, aspartate aminotransferase (AST), alanine aminotransferase (ALT), gamma-glutamyl transferase (GGT), lipase, albumin, direct bilirubin, lactate, creatinine, estimated glomerular filtration rate (eGFR)

^h^Lipids: total cholesterol, high-density lipoprotein (HDL), low-density lipoprotein (LDL), triglycerides

^i^Anthropometric measures: height, weight, body mass index (BMI), waist circumference, hip circumference, waist-to-hip ratio. At screening, only height and weight documented

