### Sample size calculation

To date there have been no studies that have investigated the benefits of improved IR in the HIV-HCV co-infected population or in HCV mono-infected patients. Studies that have investigated the effects of HCV antiviral therapy on FibroScan® score reported a 32 % reduction in mean score (10.6 +/- 4.8 kPa) compared with baseline in patients that obtained a treatment response [37]. Based on these study results, a sample size of 24 participants in each group would provide approximately 80 % power to detect a 4 kPa difference between the two treatment arms assuming a similar standard deviation. We anticipate a 20 % loss to follow-up, so an additional six participants will be randomized per group to account for loss to follow-up and to allow secondary outcome analyses. Using regression of the final measurement on the initial measurement will likely improve the power relative to using simple difference scores.

All analyses will be based on intention-to-treat basis and per protocol analysis. Intention-to-treat population will be defined as the set of all patients randomized.

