### Statistical analysis

As the primary outcome of this study, the influence of metformin on preventing and promoting regression of liver fibrosis in HCV antiviral treatment recipients will be assessed by transient elastography. The change in transient elastography scores (kPa) at week 48 (24 weeks post HCV therapy) between groups will be assessed using linear regression adjusted for baseline score. We will also compare the trend on fibrosis progression over the course of the study (12, 24, 36 and 48 weeks) between groups using mixed-effects regression analysis. All analyses will be based on intention-to-treat basis. A sensitivity analysis of the change at 48 weeks will be conducted using multiple imputations to include those participants who do not have 48-week follow-up scores.

The same set of analyses based on a per protocol basis will also be performed. For the analysis, which examines the outcome longitudinally, participants who terminated the assigned treatment prematurely will be censored at the time that they went off treatment.

Secondary outcome measures include: virological response rates, changes from baseline to week 48 in indirect measures of liver fibrosis (APRI), inflammatory markers, metabolic measures, anthropometric measurements, HCV and HIV viral loads, AFP levels and liver function. Linear regression adjusted for baseline score will be used to compare the outcome at week 48 between groups. Mixed-effects regression analysis will also be used to compare the trend over time between groups.

To account for potential confounding factors (i.e., HCV/HIV viral status, alcohol consumption, IR, BMI) associated with changes in liver fibrosis, a sensitivity analysis based on multivariate regression analysis will be performed.

Patient acceptability of daily long-term study treatment use will be evaluated (in arm 1 only) using the Treatment Satisfaction Questionnaire for Medication. Patient acceptability will be assessed based on change in median score from week 8 (first administration of questionnaire) to week 24 and week 48. Descriptive statistics will be used to summarize the data.

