When half (n = 30) of the participants have completed their 48-week visit, an interim analysis of efficacy will be conducted. The same technique and analytic strategy will be used to analyze the primary end point, transient elastography score (kPa) at 48 weeks. An intention-to-treat approach will be taken, linear regression adjusting for baseline score, and missing imputations to account for missing data will be used. The O’Brien-Fleming approach using the Lan-DeMets alpha spending function will be used, so that the criterion for statistical significance at the first analysis will be 0.005 and the criterion at the final analysis will be 0.048 to maintain 80 % power overall. This analysis will be supplemented by a mixed-effects regression model examining the outcome at all time points for all patients available, and adjusting for baseline values.

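### The primary outcome names three weeks, but the main test and alpha plan use week 48 only, and missing week-48 scans are treated differently at the interim and final analyses

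*Protocol article*

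**What the plan says.** **Definition of the primary outcome.** The Abstract (Methods) begins: "The primary outcome will be the change in FibroScan® score (kPa) from baseline to week 12 (start of HCV treatment"), and goes on to weeks 24 and 48. The Primary outcome section repeats the list: "from baseline to week 12 (start of HCV treatment), the end of HCV treatment (week 24) and 24 weeks post HCV treatment (week 48"). Neither place ranks the three weeks or says how significance would be shared among them.

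**Analysis of the primary outcome.** The Statistical analysis section opens with one test: "The change in transient elastography scores (kPa) at week 48 (24 weeks post HCV therapy) between groups will be assessed using linear regression". The baseline value is a covariate in that model. A mixed-effects model follows as an addition: "We will also compare the trend on fibrosis progression over the course of the study (12, 24, 36 and 48 weeks"). The interim paragraph in the same section will "analyze the primary end point, transient elastography score (kPa) at 48 weeks" and attaches both significance criteria, 0.005 and 0.048, to that endpoint.

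**Sample size.** The Sample size calculation section gives 24 per group for about 80 % power to detect 4 kPa, raised by six per group for 20 % loss. It names no week. It speaks only of regressing a final measurement on an initial one.

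**Population and missing scans.** The Sample size calculation section states: "Intention-to-treat population will be defined as the set of all patients randomized". For the final analysis, "A sensitivity analysis of the change at 48 weeks will be conducted using multiple imputations" so that people lacking a week-48 score are included. Later in the section the same imputation is something the team will consider, again as a sensitivity analysis. For the interim, under an intention-to-treat approach, "missing imputations to account for missing data will be used", and that paragraph says technique and strategy are the same as elsewhere.

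**The concern.** A reader cannot tell from the definition which result decides the trial. The three weeks also answer different questions. By the schedule in Study design and setting, week 12 reflects metformin before antivirals, week 24 the end of antivirals, and week 48 the period 24 weeks afterwards. In an open-label trial with three listed primary changes and no hierarchy, a favourable result at week 12 or 24 could be reported as meeting the primary outcome although no alpha was set aside for it.

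The second issue concerns who is in the decisive comparison. If imputation is needed to bring in participants without a week-48 score, and imputation is only a sensitivity analysis, the main final regression leaves them out while carrying an intention-to-treat label defined as everyone randomised. The loss need not be neutral. The Early termination section lists adverse events and diabetes progression needing additional medication among the grounds for withdrawal from the study, and metformin could influence both. The documents do not allow any resulting bias to be sized. The interim handles the same problem differently, so two looks that share one alpha plan would rest on different analysis sets.

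**Working it through.** **1. Reproduce the plan's figure.** Inputs from the Sample size calculation section: n = 24 per group, difference 4 kPa, SD 4.8 kPa. Two-sided 0.05 is assumed, because that section gives neither alpha nor sidedness.

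- Standard error = 4.8 × √(2/24) = 1.386; 4 / 1.386 = 2.887.
- Normal approximation: power = Φ(2.887 − 1.960) = 82.3 %.
- Two-sample t-test (noncentral t): 80.7 %. At 0.048: 80.2 %.
- Loss: 24 / (1 − 0.20) = 30 per group, 60 in total.

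The stated figure reproduces, as a calculation for one comparison.

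**2. What the alpha plan covers.** With half the information at the interim, two-sided criteria of 0.005 and 0.048 on a single endpoint give an overall error of 0.0499. The two looks at week 48 use the whole 5 %, so nothing is left for weeks 12 and 24.

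**3. If any of the three weeks could carry the claim.** Three tests at 0.048 each. The independent case is 1 − (1 − 0.048)³ = 13.7 %. Correlated cases come from simulation of three equicorrelated normal statistics. The correlations are assumptions, since the documents give none.

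| Correlation between visits | Family-wise error |
|---|---|
| 0.5 | 12.0 % |
| 0.7 | 10.5 % |
| 0.8 | 9.5 % |
| 0.9 | 8.0 % |

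**4. What three primary time points would cost if done properly.**

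- Bonferroni, 0.05 / 3 = 0.0167: power with 24 per group falls to 65.6 % (t-test), and 80 % power needs 32 evaluable per group.
- All three weeks required to be significant at 0.05, with a true 4 kPa difference at each: power is about 65 % at correlation 0.5 and 75 % at 0.9.

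The plan provides for neither.

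**5. Missing week-48 scans.** At the planned loss, 0.20 × 60 = 12 randomised participants would have no week-48 score.

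| Look | Main week-48 analysis | Role of imputation |
|---|---|---|
| Interim | Regression adjusted for baseline, intention-to-treat | Part of the main analysis |
| Final | Regression adjusted for baseline, intention-to-treat | Sensitivity analysis only |

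These rows cannot both follow one strategy.

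**The case against.** The best defence is that the analysis text already settles the matter. It specifies one regression at week 48, calls that score the primary endpoint, and ties both significance criteria to it, so the Primary outcome section can be read as a list of assessment times. On that reading nobody plans three tests, and the 8 to 12 % is hypothetical. This stands in part: the error figures are conditional and do not describe the planned test. It does not remove the conflict, because the Abstract and the Primary outcome section are where the primary outcome is defined, and they name three weeks.

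On missing data, the defence is that no sentence excludes anyone from the final regression, that imputation is planned, that the inflation to 30 per group protects power, and that an unseen analysis plan may hold the detail. The exclusion is indeed an inference, and power is protected. But the document itself gives imputation different roles at the two looks while claiming a common strategy, and protecting power does not make a completers' comparison an analysis of all randomised.

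A reader might also infer more than the documents support:

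- *That the interim drops participants without a scan.* It does not; it imputes, and adds a mixed model on all available patients.
- *That the power statement is for week 48.* The wording about a final measurement suggests this, but no week is given.
- *That week 48 is analysed in isolation.* A mixed model over weeks 12 to 48 is planned and can use partial follow-up, though as an additional comparison of trend.
- *That a mixed model would surely gain precision.* With 20 % missing, the variance ratio for an arm's week-48 mean is [(1 − r²)/0.8 + r²]/1.25, which is 0.95 at r = 0.5 and 0.87 at r = 0.8. That 5 to 13 % gain requires every participant missing week 48 to have a week-36 scan, so it is a best case, and r is assumed.

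**Conclusion.** Two inconsistencies hold.

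First, the document gives two primary endpoints: change at weeks 12, 24 and 48 in the definition, and week 48 alone in the main regression and the significance criteria. The sample size fits a single comparison (80.7 % power by t-test, assuming two-sided 0.05). Family-wise error of about 8 to 12 % would arise only if any one of the three weeks could carry the claim at 0.048, under assumed correlations of 0.9 to 0.5.

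Second, the final week-48 regression is labelled intention-to-treat on all randomised but, by implication, leaves out those without a week-48 score, about 12 of 60 if the planned loss occurs. The interim imputes for them in its main analysis.

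The sample size is not wrong and nothing here calls for a larger trial. Since the first point decides which result answers the trial's question, both should be settled before outcome data are examined.

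**What to change.** 1. In the Abstract and the Primary outcome section, name one primary endpoint: change in FibroScan kPa from baseline to week 48. Move weeks 12 and 24 to the secondary outcomes. State in the Sample size calculation section that the 4 kPa difference refers to week 48.
2. Choose one missing-data approach for the primary week-48 comparison, keeping all randomised participants in as far as possible, and use it at both interim and final. Either of these would do:
   - multiple imputation using the scans Table 1 already schedules at weeks 12, 24 and 36, followed by the baseline-adjusted regression; or
   - a mixed model with visit as a category and a week-48 contrast between arms. This is not the trend model now described, so it would have to be specified.
3. Make the imputation sentences in the Statistical analysis section agree with that choice.

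Cost: changes of wording, with the registry entry checked for agreement; no new data and no change in sample size. Weeks 12 and 24 can no longer be claimed as primary. If the mixed model is chosen, participants with partial follow-up contribute at the interim, so the information fraction need not be one half and the 0.005 and 0.048 criteria must be rechecked.
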